# Prophylactic nimodipine treatment for hearing preservation after vestibular schwannoma surgery: study protocol of a randomized multi-center phase III trial—AkniPro 2

**DOI:** 10.1186/s13063-021-05417-z

**Published:** 2021-07-22

**Keywords:** Nimodipine, Hearing preservation, Vestibular schwannoma, Acoustic neuroma

## Abstract

**Background:**

A previously performed phase III trial on 112 subjects investigating prophylactic nimodipine treatment in vestibular schwannoma (VS) surgery showed no clear beneficial effects on preservation of facial and cochlear nerve functions, though it should be considered that protection of facial nerve function was the primary outcome. However, the risk for postoperative hearing loss was halved in the nimodipine group compared to the control group (OR 0.49; 95% CI 0.18–1.30; p = 0.15). Accordingly, this phase III extension trial investigates the efficacy and safety of prophylactic nimodipine for hearing preservation in VS surgery.

**Methods:**

This is a randomized, multi-center, two-armed, open-label phase III trial with blinded expert review and two-stage with interim analysis. Three hundred thirty-six adults with the indication for microsurgical removal of VS (Koos I–IV) and serviceable preoperative hearing (Gardner-Robertson scale (GR) 1–3) are assigned to either the therapy (intravenous nimodipine 1–2 mg/h from the day before surgery until the fifth postoperative day and standard of care) or the control group (surgery only and standard of care). The primary endpoint of the trial is postoperative cochlear nerve function measured before discharge according to GR 1–3 versus GR 4–5 (binary). Hearing function will be determined by pre- and postoperative audiometry with speech discrimination, which will be evaluated by a blinded expert reviewer. Furthermore, patient-reported outcomes using standardized questionnaires will be analyzed.

**Discussion:**

Prophylactic parenteral nimodipine treatment may have a positive effect on hearing preservation in VS surgery and would improve patient’s quality of life. Further secondary analyses are planned. Except for dose-depending hypotension, nimodipine is known as a safe drug. In the future, prophylactic nimodipine treatment may be recommended as a routine medication in VS surgery. VS can be considered as an ideal model for clinical evaluation of neuroprotection, since hearing outcome can be classified by well-recognized criteria. The beneficial effect of nimodipine may be transferable to other surgical procedures with nerves at risk and may have impact on basic research.

**Trial registration:**

EudraCT 2019-002317-19, DRKS00019107. 8th May 2020.

## Background

Vestibular schwannomas (VS) are benign tumors, which comprise 6–8% of all intracranial tumors with an overall incidence of 1–2/100,000/year [1]. The most prevalent symptoms in patients suffering from VS are hearing loss, tinnitus, and vertigo. Disease management options include follow-up by magnet resonance imaging (MRI), stereotactic radiosurgery, and microsurgical removal.

However, the goal of modern VS surgery is total tumor removal with preservation of facial and cochlear nerve function. Deterioration of cochlear nerve functions is a common complication following VS surgery. Except for dexamethasone, there is a lack of neuroprotective medication in neurosurgical interventions. Nimodipine, a dihydropyridine calcium antagonist, is a generally well-tolerated drug with a long history in neurosurgical practice. Besides preventing cerebral vasospasm, a neuroprotective effect has been assumed [2]. Further, basic research points to an underlying neuroprotective mechanism of nimodipine [3–6]. Herzfeld et al. demonstrated a reduction of apoptosis in nimodipine-treated neuro2a cells via surgery-like stress models [4, 5]. Several monocenter, retro- and prospective clinical trials pointed to a beneficial effect of nimodipine on the long-term outcome of cranial nerve functions following VS surgery [7–14]. A monocentric pilot study on 30 subjects showed a superiority of its prophylactic administration compared to an intraoperative start or no treatment [9]. A subsequently performed phase III trial on 112 subjects with facial nerve function 12 months after surgery as primary outcome showed no clear beneficial effects [15]. But, the risk for postoperative hearing loss was halved in the treatment group compared to the control group (OR = 0.49; 95% CI 0.18–1.30; p = 0.15), particularly in medium- to large-sized tumors (Koos III/IV) [15]. However, a subsequently performed combined analysis of the phase III trial and its pilot study showed significantly lower risks for hearing loss in the treatment group, for all tumor sizes (OR = 0.38; 95% CI 0.17–0.83; p = 0.016) [16]. In Germany, nimodipine is occasionally used in VS surgery (off-label use); however, sufficient evidence by randomized controlled trials of a clear neuroprotective efficacy is still missing. Therefore, the main aim of the study is to clarify whether prophylactic nimodipine preserves hearing in vestibular schwannoma surgery.

## Methods/design

### Objectives

This trial investigates the efficacy and safety of prophylactic nimodipine for hearing preservation in VS surgery.

Preservation of hearing using prophylactic nimodipine would significantly improve the patient’s quality of life. In the future, prophylactic nimodipine treatment may be recommended as a routine medication in VS surgery. VS can be considered as an ideal model for clinical evaluation of neuroprotection, since the hearing outcome can be classified by well-recognized criteria (Gardner-Robertson scale (GR)) [17]. The primary objective is to assess the effect of prophylactic parenteral preoperatively starting nimodipine treatment for hearing preservation after VS surgery in comparison to standard care only. This will be measured by pure-tone and speech audiometry during the postoperative hospital stay. The primary endpoint is postoperative cochlear nerve function measured before discharge according to GR scale 1–3 versus GR 4–5 (binary), a suitable predictor for the preservation of serviceable hearing. The beneficial effect of nimodipine may be transferable to other surgical procedures with nerves at risk.

### Trial design

The trial will be randomized two-armed, open-label, with blinded expert review and interim analysis.

## Methods: participants, interventions, and outcomes

### Study setting

The clinical trial will be carried out in a multi-center fashion at currently 8 trial sites in Germany—mainly academic hospitals as well as a community clinic; for a list, refer to https://www.drks.de (ID DRKS00019107). The participating sites have a large expertise in VS surgery and also in nimodipine treatment. All sites are experienced in conducting GCP-conform clinical trials. Several trial sites had already participated in the previous multi-center trial [15]. Additional qualified trial sites can be included during trial conduct if necessary.

For data management, monitoring, safety management, biostatistics, and project management, the Coordinating Investigator will be supported by the Coordination Centre for Clinical Trials (CCT/KKS Halle), which has comprehensive experience with drug trials. This trial with its protocol is approved by the German Competent Authority and the Ethics Committees of each site and is registered at https://www.drks.de (ID DRKS00019107).

### Eligibility criteria

Patients with VS, indication for surgery, and preoperative serviceable hearing (GR 1–3) will be enrolled. Based on the data of both previous trials [9, 15, 16], patients suffering from VS of all tumor sizes will participate. However, patients with neurofibromatosis and previous therapy (surgery and/or radiotherapy) are excluded.

#### Inclusion criteria

Adults age ≥ 18 yearsVS (Koos I–IV) with indication for surgeryPreoperative pure-tone audiogram (not older than 3 months prior to surgery), hearing function according to GR 1–3 (air conduction pure-tone average (PTA) (0.5–3 kHz) < 90 dB hearing level (HL))Preoperative MRI (not older than 6 months prior to surgery)Written informed consent obtained according to international guidelines and local lawsAbility to understand and give informed consentSafe contraception measures for males and females

#### Exclusion criteria

Hearing function GR 4–5 (air conduction PTA (0.5–3 kHz) ≥ 90 dB HL)Conductive hearing loss at the affected side (mean air bone gap (0.5, 1, 2, 3 kHz) > 10 dB) if bone conduction is measurablePreviously irradiated or surgical treated VSNeurofibromatosis, other brain tumors, other reasons for inoperabilityPregnancy and lactation periodKnown hypersensitivity to nimodipine or any of the excipients (ethanol, Macrogol, sodium citrate, citric acid) to be used for nimodipine infusionHistory of (reformed alcoholics) or persistent abuse of alcoholKnown current kidney or liver insufficiencyAny medical condition that in the opinion of the investigator would not permit participation in the clinical trialUnstable angina pectoris and/or myocardial infarction during the last 4 weeks before the start of treatmentSevere, uncontrolled, symptomatic hypotension at inclusionSubjects with psychological, psychiatric, neurological, familial, sociological, or geographical conditions that do not permit compliance with the protocol as well as officially and/or legally accommodated personsParticipation in another interventional trial simultaneously and within the last 30 days prior to inclusion (registries or observational studies allowed)

### Discontinuation criteria and dropouts

Patients can have treatment or trial participation terminated prematurely at any time, without having to give reasons. If the patient agrees, the visits, follow-up, and documentation will continue as scheduled. Further reasons for discontinuation are the occurrence of adverse events related to the study treatment that cannot be treated adequately or of adverse events which in the opinion of the investigator make it necessary to stop the study treatment. The investigator may also terminate the study participating for the patient in case of missing compliance or other circumstances which make trial-relevant follow-up impossible. The sponsor might also decide to withdraw a patient from trial participation (the reason has to be specified, e.g., major protocol violation).

If a patient decides to discontinue the study after randomization but before the respective start of treatment, the patient will be considered as a dropout.

### Interventions

Patients will be randomized and assigned to one of two groups (interventional or control group).

#### Control group

Patients in the control group will receive surgery only, as the standard of care, and be prepared, operated, and treated afterwards as is required by routine procedures at the trial site. Nimodipine administration is not allowed in control patients for the whole trial duration except in case of emergency of aneurysmal subarachnoid hemorrhage (SAH).

#### Interventional group

Patients assigned to the interventional group will receive nimodipine parenterally from the day before surgery until the 5th postoperative day additional to surgery as standard care. Nimodipine should be given as soon as possible on the day before surgery. However, due to the clinical situation, a defined time was not determined. Administration of nimodipine will be started via a peripheral venous access with a dosage of 1 mg/h (5 ml/h) for at least 2 h. If nimodipine is well tolerated, the dosage should be increased to 2 mg/h (10 ml/h). During and after surgery, nimodipine should be administered via a routine central line. Blood pressure should be monitored three times a day due to the effects of and on nimodipine. In case of hypotension, a dose reduction of 1 mg/h or 0.5 mg/h or a stop of treatment is intended. The administration of nimodipine and thus the cumulative dosage will be documented for each patient. Afterward, until the patient’s end of study, nimodipine treatment is not permitted except in case of emergency of aneurysmal SAH.

Nimodipine will be purchased by Bayer Vital GmbH, Leverkusen, Germany.

#### Treatment modification

Dose reduction is essential in the case of symptomatic patients caused by hypotension, e.g., dizziness and fatigue. An initial dose reduction from 2 mg/h (10 ml/h) to 1 mg/h (5 ml/h) is recommended. Thereafter, the dose should be reduced to 0.5 mg/h (2.5 ml/h) if the patient is still symptomatic. Nimodipine treatment may also be discontinued. However, dose reduction/discontinuation due to other adverse events as well as rechallenge of nimodipine will be the investigator’s discretion. All dosages administered to the patient and any dose change or interruption will be recorded.

### Outcomes

#### Primary outcome

The primary endpoint is postoperative cochlear nerve function measured before hospital discharge according to GR 1–3 versus GR 4–5 (binary). This outcome defines the preservation of useful hearing.

#### Secondary outcomes

The secondary endpoints are the following:
Late postoperative cochlear nerve function measured at follow-up 3 to 6 months after surgery according to GR 1–3 versus GR 4–5 (binary)Postoperative deterioration of cochlear nerve function of at least one grade according to the GR compared with its preoperative function (binary)Late postoperative deterioration of cochlear nerve function of at least one grade according to the GR compared with its preoperative function measured at follow-up 3 to 6 months after surgery (binary)Change of pure-tone thresholds (PTA) and speech discrimination score (Word Recognition Score, WRSmax)GR and American Academy of Otolaryngology-Head and Neck Surgery (AAOHNS) scoresIntraoperative deterioration of brainstem audiometry evoked potential (BAEP) mean values (amplitudes and latencies)Subjective quality of life/psychosocial impairment will be assessed by the means of three patient’s questionnaires (Hearing Handicap Inventory for the Elderly (HHIE), Short Form (SF)-12, Penn Acoustic Neuroma Quality of Life (PANQOL)) before surgery and at follow-upAnatomical preservation of the cochlear nerve and preservation of wave V (BAEP)Safety data

### Participant timeline

Duration of intervention: 7 days

Duration of follow-up: 3 to 6 months

Study related: estimated start 4th quarter 2020. Duration of enrolment: 21 months, interim analysis, 21 months. Estimated end of the trial: 2025

A detailed visit schedule and trial flow chart is provided (Figs. 1 and 2). The schedule lists all of the evaluations in tabular form and indicates with an “X” when they have to be performed.

**Fig. 1 Fig1:**
[figure not shown]
Flow chart

**Fig. 2 Fig2:**
[figure not shown]
Visit schedule and assessments

### Sample size

The sample size calculation is based on the combined results of the pilot study and the multi-center study regarding the primary outcome postoperative cochlear nerve function [9, 15, 16]. Considering patients with tumor size Koos I–IV and preoperative hearing function GR 1–3, 30 out of 46 patients (65.2%) suffered from deaf in the control group versus 31 out of 63 patients (49.2%) in the therapy group. Using these frequencies, based on a two-sided chi-square test with alpha = 5% and 80% power and an interim analysis at information fraction 0.5 with O’Brien-Fleming-type alpha-spending and possible trial stop because of futility, requires 80 patients per group in the first stage. Additional 79 patients per group are necessary if the trial is not stopped because of futility after the interim analysis (SAS® procedure SEQDESIGN). Assuming a dropout rate of 5%, the planned sample size for the trial is 84 patients per treatment group in the first stage and 84 additional patients per group in the second stage. Finally, the total maximum number of patients required for both stages is 336 (168 before interim analysis and 168 after interim analysis).

### Recruitment

Each site will screen their VS patients with indication for surgery for recruiting. Inclusion of all tumor sizes (Koos I–IV) [18] and the close patient-physician relationship in this indication will facilitate recruitment. To date, 4 study centers which have already participated in the previous study with high recruitment rates and 4 additional trial sites with good VS surgery and clinical trial reputation will participate. All sites had committed their planned recruitment via feasibility questionnaires. In the previous trial [15], recruitment was completed even faster than planned, so recruitment is expected to be feasible again without delay.

## Methods: assignment of interventions

### Allocation

To ensure concealment of treatment allocation, stratified block randomization with respect to tumor size (Koos I/II vs. III/IV) and variable block length will be performed centrally in SAS and included in SecuTrail for Internet-based online randomization independently organized by CCT Halle.

### Blinding

A double-blind design, usually the favorable approach in clinical research, has not been proven as feasible for several reasons. From an ethical point of view, a double-blind approach using a placebo would require a central-line catheter for 5 days in the postoperative course in patients of the control group. Furthermore, manufacturing of an appropriate i.v. placebo is not feasible.

## Methods: data collection, management, and analysis

### Data collection methods

#### Tumor size and extent of resection

Tumor size is determined by MRI (thin-slice, axial T1-weighted with and without contrast enhancement, not older than 6 months prior to surgery) and classified according to Koos grading system [18] by the investigator of each trial site (Koos I/II vs. III/IV) for the stratified randomization. For statistical analysis, it is additionally evaluated by a blinded independent expert. The extent of resection will be evaluated by the investigator’s subjective impression intraoperatively and by an independent expert via MRI.

#### Audiometry/GR evaluation

Standard pure-tone audiometry provides diagnostic information concerning the degree, type, and configuration of hearing loss. Audiometries should be performed in a soundproof booth. Parameters are defined in International Organization for Standardization (ISO) norm (ISO 11957:1996, 1996). Speech audiometry is performed to obtain the speech recognition threshold by using German multisyllabic words (“Freiburger Zahlentest”), if possible, and suprathreshold speech recognition by using German monosyllabic words (“Freiburger Einsilbertest”), if possible. The following information should be provided additionally regarding the performed pure-tone and speech audiometries for both ears in each patient:
Pure-tone thresholds for air conduction at frequencies of 0.25, 0.5, 1, 2, 3, 4, and 8 kHz. Masking has to be applied if needed.Pure-tone thresholds for bone conduction at frequencies of 0.5, 1, 2, 3, 4, and 6 kHz. Masking has to be applied if needed.The graph plotted by connecting all hearing threshold values for all tested frequencies as well as masking levels used.Speech reception threshold (SRT) for air conduction (ipsilateral headphone-presentation, “Freiburger Zahlentest”).If SRT < 65 dB sound pressure level (SPL): word recognition score for Freiburger Monosyllables at 65, 80, and 95 dB SPL, using 2 lists each, masking levels have to be reported.If SRT ≥ 65 dB SPL and SRT < 80 dB SPL: word recognition score for Freiburger Monosyllables at 80 and 95 dB SPL, using 2 lists each, masking levels have to be reported.If SRT ≥ 80 dB SPL: word recognition score for Freiburger Monosyllables at 95 dB SPL, using 2 lists, masking levels have to be reported.

GR evaluation: Hearing class is determined according to the GR grading system [17] by the investigator of each trial site for inclusion. If speech discrimination (WRS_max_) is not available, evaluation will be done by pure-tone measurements only. For statistical analysis, it is additionally evaluated by an independent expert. AAOHNS evaluation will only be done by a blinded expert [19].

If during surgery the nervus cochlearis has been cut, grading is considered as GR 5. In this case, postoperative audiometries do not have to be performed.

#### Questionnaires

Patients are asked for an evaluation of subjective health and communication competencies (quality of life) via three different patient questionnaires (SF-12 [20, 21], PANQOL [22], HHIE [23, 24]) twice during the trial: before surgery and during follow-up after 3 to 6 months. Interpretation of questionnaires and calculation of scores is highly standardized but will nevertheless be done by a blinded expert.

### Data management

All data will be entered directly at the trial site by the study team via remote data entry in the trial-specific electronic Case Report Form (eCRF). The study management software secuTrial®, a Good Clinical Practice (GCP)-compliant clinical data management system for the conduction of clinical trials, will be used for data entry and query management. Management of the study data base will be done by CCT Halle.

In a multistage procedure, the obtained data will be checked electronically for their plausibility and consistency by CCT Halle. In case of implausible or missing data, queries will be generated and provided to the investigator in order to obtain any missing information and resolve inconsistencies.

After completion of data capture and quality check, data base will be closed by CCT Halle and the data will be transferred to the biometrician for statistical analysis.

### Statistical methods

#### Populations for analysis

The primary analysis data set is the modified intention-to-treat population. This data set contains all the patients who have been enrolled in the clinical trial, randomized, and treated by surgery with pre- and postoperative values of the nervus cochlearis and tumor size.

The secondary analysis data set is derived from the per-protocol population. This data set includes all patients of the primary analysis data set without major inclusion/exclusion violations who have been treated according to their randomization schedule: For patients in the nimodipine group, this requires nimodipine treatment at least 18 h per day (with any dosis) from day −1 (day before surgery) until day 5 after surgery (in total 7 days); patients in the control group having received nimodipine will be excluded.

The tertiary analysis data set (safety population) contains all the patients who underwent surgery and/or received at least one dose of the study medication.

#### Evaluability of a subject

Patients are evaluable if pre- and postoperative values of the nervus cochlearis and the tumor size are available.

#### Final analysis

##### Primary endpoint

The primary efficacy analysis will be performed according to the intent-to-treat principle. Because of the expected very small number of dropouts (less than 5%), missing outcomes will be excluded from the analysis. To test the superiority of the intervention versus the control group, logistic regression will be used with the treatment group and tumor size (because of stratified randomization w.r.t. tumor size) as variables. Results will be presented as odds ratios including 95% Wald confidence intervals and p-values.

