##### Secondary endpoints

Additional sensitivity analysis will be performed by a per-protocol analysis for the primary endpoint. The risk difference of postoperative hearing deterioration will be supplemented by a 95% Wald confidence interval, and the Mantel-Haenszel estimation (with tumor size according to Koos as strata variable) will be performed as a sensitivity analysis as well as an additional per-protocol analysis. The secondary outcome postoperative deterioration of cochlear nerve function of at least one grade according to the GR compared with its preoperative function will be analyzed similar to the primary outcome and results will be given as odds ratios including 95% Wald confidence intervals and p-values. Deterioration of BAEPs amplitudes and latencies of the intraoperative BAEP will be evaluated by comparing their differences between beginning and end of surgery using linear regression with covariates treatment group and tumor size (Koos I/II or Koos III/IV). Change in quality of life (SF-12, PANQOL, HHIE) will be also evaluated using linear regression with covariates treatment group and tumor size (Koos I/II or Koos III/IV). All analyses of secondary endpoints will be interpreted in an exploratory sense.

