##### Methods for additional analyses, such as subgroup analyses and adjusted analyses

Additionally, logistic regression analyses of the primary endpoint adjusted for tumor size (Koos classification and volumetry), preoperative hearing, extent of resection, positioning of the patient during surgery (semi-sitting or supine), total dose of nimodipine, dose modification (yes/no), and intraoperative events, e.g., bleedings (yes/no), as well as subgroup analyses by the following subgroups are planned:
Preservation of cochlear nerve intraoperative by surgeons’ statement (yes/no)Cystic tumor by blinded expert evaluation (yes/no)SexBAEP (amplitude and latency: stable/worsened/totally lost)

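### Adding preoperative hearing to the primary logistic model would be a near-costless improvement; the plan leaves it to additional analyses

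*Protocol article*

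**What the plan says.** All references are to the protocol article.

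- **Final analysis, Primary endpoint:** "logistic regression will be used with the treatment group and tumor size (because of stratified randomization w.r.t. tumor size) as variables". The model is written out, with the stratified randomisation given as the reason for the one covariate.
- **Allocation:** "stratified block randomization with respect to tumor size (Koos I/II vs. III/IV) and variable block length". Tumor size is the only stratification factor named.
- **Primary outcome:** postoperative GR grade before discharge, split between grades 3 and 4.
- **Inclusion criteria:** a preoperative audiogram showing GR 1 to 3 is required for entry.
- **Evaluability of a subject:** "Patients are evaluable if pre- and postoperative values of the nervus cochlearis and the tumor size are available". The section Populations for analysis sets the same condition for the primary analysis set.
- **Methods for additional analyses:** the article plans "logistic regression analyses of the primary endpoint adjusted for tumor size (Koos classification and volumetry), preoperative hearing, extent of resection". The same list continues with patient positioning, total nimodipine dose, dose modification and intraoperative events.

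**The concern.** Patients enter at GR 1, 2 or 3 and fail at GR 4 or 5, so a GR 3 patient may fail by losing one grade while a GR 1 patient has further to fall. The starting grade is therefore a natural candidate predictor. It is complete by definition in the primary analysis set, yet neither the stratification nor the primary model uses it.

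Two things are at stake. If the starting grade is prognostic, adjusting for it raises power at the same sample size. If the arms differ in it by chance, the planned model shifts the treatment odds ratio, and in an open-label trial that would be an obvious challenge to the result. Choosing the covariate after seeing the data would not answer that challenge.

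The additional analyses only partly help. Extent of resection, total dose, dose modification and intraoperative events arise after randomisation and may be affected by treatment. A model containing them does not estimate the same treatment effect.

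**Working it through.** **Inputs from the article (Sample size).** "30 out of 46 patients (65.2%) suffered from deaf in the control group versus 31 out of 63 patients (49.2%) in the therapy group"; two-sided alpha 5%, power 80%, one interim at information fraction 0.5, 80 + 79 = 159 evaluable per group, 5% dropout.

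**Assumed, because the article gives no figure.** GR 1/2/3 mix 35/40/25%; 60% Koos III/IV; log-odds 0.8 for Koos III/IV; odds ratio (OR) of deafness per GR grade ranged from 1 to 4.

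**1. The plan's own sample size.** The rates are 30/46 = 0.6522 and 31/63 = 0.4921, with difference 0.1601 and mean 0.5721.

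Fixed design: n = (1.960 + 0.8416)² × 2 × 0.5721 × 0.4279 / 0.1601² = 149.9 per group.

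O'Brien-Fleming-type alpha spending (bounds 2.772 and 1.979), with an assumed O'Brien-Fleming-type non-binding futility bound, inflates this by 1.0607: 149.9 × 1.0607 = 159.0. The article has 159. Then 159/0.95 = 167.4, rounded up to 168 per group, or 336 in total. The sample size reproduces without the extra covariate.

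**2. Power with and without preoperative GR.** Data were generated from logit P(deaf) = a(arm) + 0.8 × [Koos III/IV] + log(OR) × grade, with grade coded −1, 0, 1. The two intercepts were solved so that the marginal rates stay at 65.2% and 49.2%. There were 159 patients per group, 4000 data sets per row, a two-sided 5% Wald test and no interim look.

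| OR per grade | Control deaf at GR 1/2/3 | Treatment + Koos | + GR class | Gain (points) |
|---|---|---|---|---|
| 1 | 65/65/65% | 85.0% | 84.7% | −0.3 |
| 1.5 | 57/66/75% | 83.5% | 84.4% | 0.9 |
| 2 | 52/68/80% | 84.6% | 86.4% | 1.8 |
| 3 | 44/70/87% | 84.5% | 89.0% | 4.5 |
| 4 | 40/72/91% | 83.2% | 90.1% | 6.9 |

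The Monte Carlo standard error of one entry is about √(0.85 × 0.15/4000) = 0.6 points. These are single-look figures, so the two columns should be compared with each other and not with the 80% of the group-sequential design.

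Other assumptions give the same picture. With 146 per arm and a GR mix of 40/35/25%, power goes from 81.1% to 82.1% at OR 1.65, from 81.7% to 84.9% at OR 2.5, and from 80.3% to 87.0% at OR 3.3. A further simulation at 159 per arm gave 83.5% against 83.3% with no prognostic effect, and a gain of about 6 points at OR 3.

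With no treatment effect, type I error was 5.0% (planned) and 4.9% (adjusted) at OR 2, and 5.0% and 5.2% at OR 3. Both tests are valid.

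**3. Chance imbalance.** Variance of grade = (0.35 + 0.25) − (−0.35 + 0.25)² = 0.59, so SD = 0.768. The SD of the difference in mean grade is 0.768 × √(2/159) = 0.086. There was no treatment effect, the imbalance was held fixed, and 3000 data sets were run per case. At 2 SD the GR 1/2/3 counts are 62/64/33 in control and 49/63/47 under nimodipine.

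| OR per grade | Imbalance | Planned: mean OR, type I error | Adjusted: mean OR, type I error |
|---|---|---|---|
| 1.5 | 2 SD | 1.07, 5.5% | 1.00, 4.4% |
| 2 | 2 SD | 1.11, 6.9% | 0.99, 5.2% |
| 3 | 2 SD | 1.19, 9.2% | 1.01, 5.0% |

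At 1 SD the planned model's mean OR is 1.04, 1.05 and 1.09, and its error stays at 4.5 to 5.1%. The test is disturbed only by a large imbalance, but the estimate moves in every case.

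**4. What the odds ratio means.** The marginal treatment OR is (31/32)/(30/16) = 0.517. Conditional on Koos and GR it is 0.497, 0.483, 0.455 and 0.430 at OR 1.5, 2, 3 and 4 per grade. The same treatment effect thus reads as a stronger odds ratio after adjustment, which has to be said in the plan.

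**The case against.** The strongest reply is that nothing here is wrong. The model adjusts for the stratification factor and says why, the sample size rests on an unadjusted chi-square test, and the promised power is met. That stands. A reader might infer that the trial is underpowered or its primary test flawed; steps 1 and 2 show neither.

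A reader might also infer that the plan ignores preoperative hearing, or adjusts for it only in one joint model with post-randomisation variables. The article supports neither reading. It does list preoperative hearing, it speaks of analyses in the plural, and it does not say that all listed variables enter together. The full protocol or analysis plan may divide them. What remains is that the article does not clearly fix a model with treatment, Koos and preoperative hearing alone, and that the confirmatory test goes without the covariate.

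The prognostic strength is assumed. The section Audiometry/GR evaluation also grades any cut cochlear nerve as GR 5 whatever the starting grade, so distance from the cut-off does not describe every failure. This too stands, and it is why the gain is given as a range starting near zero.

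Two extensions are tempting and do not hold. The one-grade deterioration endpoint "will be analyzed similar to the primary outcome", but it is defined against each patient's own preoperative grade and is exploratory, so it cannot be said to ignore the starting grade. The lack of a trial-site term is a separate preference on which nothing here bears.

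**Conclusion.** The point holds as an optional improvement, not as an error. The primary model leaves out a complete baseline measure of the outcome scale that the randomisation does not balance. At the same sample size, including it would add about 0 to 2 points of power at an OR of 1.5 to 2 per grade and 4 to 7 points at 3 to 4, with essentially no loss if the grade is uninformative. It would also keep the treatment estimate near its true value when the arms differ in preoperative hearing by chance.

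The direction rests on preoperative hearing being prognostic at all. The size rests on the assumed GR mix, Koos mix and OR per grade, none of which the article reports.

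**What to change.** Prespecify the primary model as treatment group + randomisation Koos stratum + preoperative hearing.

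- Name one form of preoperative hearing, for example the continuous preoperative pure-tone average, or the blinded expert's preoperative GR grade. If the grade is chosen, say how a patient is coded whom the expert places outside GR 1 to 3, since the investigator's grade decides inclusion.
- State that the odds ratio is conditional on the covariates, and keep the Koos-stratified risk difference already planned as the marginal summary.
- Keep extent of resection, total dose, dose modification and intraoperative events out of any model that is meant to estimate the treatment effect. Label models that contain them as descriptive.

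The cost is a change of analysis wording before outcome data are seen. No new measurement and no more patients are needed, because preoperative hearing is already required for entry and for evaluability. The price is an odds ratio conditional on one more covariate, and so less directly comparable with unadjusted results.
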